## TOES PROTOCOL: A STUDY OF TOLERANCE TO ELECTRICAL MUSCLE STIMULATION IN COPD PATIENTS

A study of the clinical tolerance, the cardio-respiratory response and the muscular fatigue induced by a session of electrical muscular stimulation in COPD patients

Authors: [name]

[name]

[name]

[name]

[name]

1. **Introduction**

Chronic Obstructive Pulmonary Disease (COPD) is a major cause of morbidity and mortality around the world and is associated with high health costs. Patient death is not solely due to loss of respiratory function but extra-pulmonary pathologies such as cardiovascular disease [1], osteoporosis, and depression [3] also contribute to the overall picture of the disease.

One systemic effect, muscular dysfunction is a key consequence of COPD. We now know that muscular weakness is associated with shorter survival, increased medico-economic costs [4, 5] and is a negative prognostic marker independent of the degree of respiratory malfunction [6]. Muscular dysfunction also contributes to a poor functional status [7] and a lower quality of life for these patients [8].

Rehabilitation to exercise is nowadays recognized as the best treatment modality able to improve functional ability to exercise and the quality of life of patients presenting moderate to severe COPD [9]. However, an improvement in aerobic fitness, which governs an individual’s fitness [10], does not have much effect on improving muscular weakness and muscular atrophy. A number of authors have therefore recommended that more emphasize is given to rebuilding muscular strength. Amongst the modalities of muscular rehabilitation, the localised exercise of muscles by electrical stimulation has been studied in COPD patients by several authors [11-15]. These studies show that this type of training has benefits for COPD patients, in terms of strengthening muscles, increasing functional abilities and improving quality of life, including for some COPD patients with chronic respiratory failure.

Electrical muscle stimulation has the advantage of specifically and locally targeting a chosen muscular group. Furthermore, the apparatus is light and manageable, easy to transport and can be used by the patient by-himself. Above all, the use of electrical muscle stimulation for patients with moderate to severe COPD is based on the hypothesis that it requires minimal respiratory effort while being carried out. Electrical muscle stimulation therefore seems to be an ideal therapy for the rehabilitation of patients who suffer from severe respiratory difficulties when doing physical exercise [16].

Nevertheless, our experience (ESTIM protocol, CER #20105) shows that some patients experience difficulties in increasing the intensity of stimulation, even after several weeks of training thus limiting the treatment’s effect [17]. However, the cardio-respiratory response of a COPD patient during a session of electrical muscle stimulation has never been described. Theurel’s study, carried out with healthy subjects, suggests that minute ventilation increases significantly more when the intensity of the electric stimulation is increased than during voluntary exercise of equal intensity. Minute ventilation may increase to 10L/min (23 ± 4 vs 13 ± 3 L/min at rest) when the intensity reaches 50% of the maximal voluntary contraction [18]. Furthermore, this study shows that oxygen consumption and heart rate increase with time and intensity during a session of electrical muscle stimulation. These factors could limit the ability for patients to tolerate electrical muscle stimulation in the same way as a decrease in oxygen saturation, and are worth investigating. What is more, the abilities to produce and to tolerate muscular contraction at a given stimulation intensity vary greatly for one individual and between individuals [19, 20] particularly for thinner individuals [14]. Body composition, especially at the site of stimulation, could influence the transmission of the electric stimulation and therefore could be partly responsible for intolerance to electrical muscle stimulation. Finally, there is currently no data concerning induced muscular fatigue and the metabolic expenditure associated with a complete session of electrical muscle stimulation in COPD patients. This type of information could help determine the minimum delay to respect between two sessions of electrical muscle stimulation in order to allow optimal muscular recovery in patients and improve long-term tolerance to a course of electrical muscle stimulation.

We therefore propose to evaluate COPD patient tolerance to electrical muscle stimulation together with the cardio-respiratory response, the symptoms linked to exercise (daily exercise, maximal exercise) and felt during the electrical muscle stimulation itself (pain perception), body composition, and the muscle fatigue which follows a stimulation session.

This study will allow us to describe the muscular and cardio-respiratory physiological responses associated with this type of training session with the aim of better adapting electrical muscle stimulation programmes to COPD patients according of their clinical tolerance.

**Objectives**:

**Overall objective:**

To study the tolerance of COPD patients to electrical muscle stimulation (EMS) (the ability to increase the intensity during one session and over the course of several sessions).

**Specific objectives:**

1. To determine whether an increase in ventilation, an acceleration in heart rate and/or a decrease in arterial oxygen saturation during electrical muscle stimulation is/are associated with COPD patient intolerance to EMS.
2. To determine whether pain perception influences COPD patient tolerance to electrical muscle stimulation and whether it changes over the course of several EMS sessions.
3. To determine whether body composition around the quadriceps influences COPD patient tolerance to electrical muscle stimulation.

**Secondary objectives:**

1. To quantify the muscular fatigue induced by a session of electrical muscle stimulation in COPD patients.
2. To determine whether electrical muscle stimulation increases systemic inflammation and oxidative stress.

**Hypotheses:**

**Main hypothesis:**

Some COPD patients have a low tolerance to electrical muscle stimulation (small or null increase in intensity after 5 sessions).

**Specific hypotheses:**

A large increase in ventilation, an acceleration in heart rate and/or a fall in arterial oxygen saturation during electrical muscle stimulation decreases patient tolerance to EMS.

Excessive pain perception lowers tolerance to electrical muscle stimulation. Pain perception diminishes over the course of several EMS sessions when electrical muscle stimulation is applied progressively.

Low body fat around the quadriceps is associated with increased pain perception during a session of electrical muscle stimulation and is therefore associated with lower tolerance to this training modality.

**Secondary hypotheses:**

Peripheral muscular strength is reduced following electrical muscle stimulation in COPD patients (muscular fatigue).

Systemic inflammation and oxidative stress are increased after electrical muscle stimulation.

Excessive muscular fatigue and/or the increased production of inflammatory proteins could contribute to a patient’s inability to increase EMS intensity over the course of several sessions and therefore limit the effectiveness of this training modality.

1. **Protocol**

**Inclusion criteria:**

Age ≥ 40 years

Patients presenting chronic obstructive pulmonary disease (COPD) (GOLD II to IV)

Smoker or ex-smoker (10 pack years or more)

Absence of any known neuromuscular pathology

Absence of any vascular pathology (legs especially)

Absence of any skin disorders on the legs

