**Groups**:

All patients will receive the same evaluations and follow the same protocol.

We will include equal numbers of patients from different severity groups: GOLD II, III and IV.

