**Study schedule**

Participation in this study involves 3 visits. The first and second visits (V1 and V2) will be separated by a day while the third visit (V3) will occur 7 days after V2. During these 7 days, the patient will be asked to carry out 5 sessions of electrical muscle stimulation training by himself, spread out as whenever he likes. He will be given the electrical stimulator and the electrodes during V2.

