***Assessment of body composition using DEXA***

Body composition will be assessed using DEXA which allows the local quantification of bone density, lean body mass and body fat. This measure will allow us to determine the regional distribution of lean body mass vs body fat.

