***Assessment of quadriceps strength and fatigue***

All measurements will be carried out on the dominant quadriceps muscle with the patient lying on his back, with the knee at a 90º angle, in a position standardised by Man et al. [21]. For the sake of the patient’s comfort, his back can be raised by an angle of 30º relative to the horizontal.

The battery of tests includes:

1. ***Maximum voluntary strength (MVS)***

Five measurements will be carried out allowing for a recovery period of 2 minutes between contractions. Measurements must be reproducible (<10% variation). The highest measurement, sustained for at least 1.5 seconds, will be used for analytical purposes. During a voluntary muscular contraction, fatigue of the rectus femoris and the vastus lateralis muscles will be objectified in real-time using surface electromyography (Biopac System) by means of electrodes placed on the skin near each muscular head. Three EMG electrodes will be placed at the heads of the quadriceps and the muscle’s electric activity will be monitored throughout the exercise.

1. ***Quadriceps twitch force (non-cooperative force) measurements***

The strength of the dominant quadriceps will also be assessed independently of the patient’s motivation during a supramaximal magnetic stimulation of the femoral nerve. This measurement will be carried out with the patient in the supine position, his knee and hip at 45º angles, as frequently performed in our lab [7]. We have previously validated this method, demonstrating its reproducibility and sensitivity to change [7].

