***Bleep fitness test***

In order to quantify the patient’s cardio-respiratory response to maximum effort, patients will undergo an incremental bleep fitness test as frequently carried out in our lab (Pepin et al. 2005). This test uses a portable “metabograph” fitted with a telemetric system (Oxycon mobile, Viasys) to measure ventilation, oxygen consumption, heart rate and saturation throughout the exercise. Physiological values measured during a session of electrical muscle stimulation can therefore be compared to the maximal values measured during this test. Furthermore, this test will allow us to characterise the patients’ physical condition. Fifteen minutes before this test an electrocardiogram (ECG) at rest will be carried out.

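### The eligibility list has no item on implanted electronic devices or metal in the stimulated region, although every patient receives electrical and magnetic stimulation

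*Protocol*

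**What the plan says.** The list under Inclusion criteria has six items, and no exclusion list follows it. Three items set age (40 or over, with no upper limit), COPD at GOLD II to IV, and smoking history. The other three are "Absence of any known neuromuscular pathology", "Absence of any vascular pathology (legs especially" and "Absence of any skin disorders on the legs". Pacemakers, defibrillators, metal implants and joint prostheses are mentioned nowhere in the Protocol.

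Under Groups, "All patients will receive the same evaluations and follow the same protocol". Under Study schedule, "the patient will be asked to carry out 5 sessions of electrical muscle stimulation training by himself", within the seven days between the second and third visits. The section on the home sessions tells the patient to keep raising the intensity to the most he can bear. Contact in that week is by phone: one call on the day of the first home session, then as needed. The current is delivered to both thighs, with the upper electrode placed high on the thigh below the groin.

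The quadriceps test battery includes a twitch measurement "during a supramaximal magnetic stimulation of the femoral nerve". The only cardiac check is in the fitness test section: "Fifteen minutes before this test an electrocardiogram (ECG) at rest will be carried out". No decision is tied to its result.

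**The concern.** Half of the list concerns the legs or nerve and muscle function, so the sponsor did write criteria that bear on leg stimulation. Those criteria do not cover implanted electronics or metal near the electrodes. A patient paced for a conduction disorder, or one with a hip or knee prosthesis, can meet all six items and go through every procedure.

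Two things are at stake. The first is safety: possible interference with a device, above all in the home sessions, where nobody is with the patient. The second is the analysis: an acceleration in heart rate during stimulation is one of the predictors named in the first specific objective, and a rate set by a device does not measure the patient's response.

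**Working it through.** There is no stated figure to reproduce, because the point concerns eligibility wording. The check sets the sections side by side.

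1. **Does any item keep such a patient out?** Take a patient of qualifying age, COPD grade and smoking history who has a pacemaker for a conduction disorder.
   - Neuromuscular item: met.
   - Leg skin item: met.
   - Vascular item: met, since a conduction disorder is not disease of the vessels. The same holds for a joint prosthesis.
   - Result: eligible.

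2. **Does any later step catch him?** The first visit comprises consent, spirometry, the fitness test with its ECG, and familiarisation. Neither the description of that visit nor the visit chart lists a medical history. The ECG may show a paced rhythm, but no eligibility action follows from it, and it cannot show an orthopaedic implant.

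3. **Is any procedure withheld from him?** No. Groups gives all patients the same evaluations. Exposure by setting:

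| Procedure | Setting | Supervision |
|---|---|---|
| Thigh stimulation, visits 1, 2 and 3 | Hospital | Staff present |
| Thigh stimulation, 5 sessions | Home | Alone, phone contact |
| Magnetic femoral nerve stimulation | Laboratory | Staff present |

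4. **What happens to the Objective #1 predictor?** The analysis correlates ∆Intensity (V3-V2) with the cardio-respiratory response, both raw and as a percentage of the fitness-test maximum. Take the limiting case, assumed here, in which a device holds the rate at a constant r at rest, during stimulation and at maximal effort:
   - acceleration = r − r = 0, which reads as no response;
   - percentage of maximum = 100 × r / r = 100%, which reads as a maximal response.

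   The two forms of the same predictor then contradict each other, and neither describes the patient. A device that controls the rate only part of the time would distort less.

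5. **Weight of one such patient.** Sample size gives 3 × 7 = 21 patients. One patient is 1/21 = 4.8% of the whole sample and 1/7 = 14.3% of his severity group.

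**The case against.** The strongest reply is that the hazard is not in the documents. Nothing in the Protocol says that electrical or magnetic stimulation endangers a patient with a device, and the list states no safety purpose: its three leg and nerve-muscle items could equally remove confounders of fatigue and pain. This is fair, and the safety argument does rest on general knowledge about stimulation. The data argument needs less. It requires only that a device can set the heart rate and that the Protocol uses heart rate as a predictor.

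The vascular item can also be read broadly, since it singles out the legs without being confined to them. It may therefore exclude some patients with cardiovascular disease. It does not reach an isolated conduction disorder or a prosthesis. Clinical judgement at the centre, or a question on the consent pages (not available for this review), might catch such patients. The Protocol's criteria do not require it.

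A reader might infer more than the documents support:
- **That such patients are likely to present.** The introduction links COPD to cardiovascular disease, but no prevalence of devices or implants is given, so any probability of enrolling one would rest on an invented rate.
- **That an implant would distort the regional DEXA values used for Objective #3.** The DEXA section says only "This measure will allow us to determine the regional distribution of lean body mass vs body fat". The introduction suggests that body composition at the site could affect transmission of the current, but says nothing about metal.
- **That all stimulation is unsupervised.** Only the five home sessions are.
- **That a medical history at the first visit already covers the check.** None is listed.

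**Conclusion.** The gap is real and should be closed before enrolment. As written, the list admits patients with implanted electronic devices or metal in the stimulated region, and no later step is required to identify them. The safety part rests on general knowledge that stimulation may interfere with such devices. The data part rests on the assumption that an enrolled patient's heart rate is wholly or partly controlled by a device. In that case his Objective #1 heart-rate values are invalid in both forms, at a weight of 4.8% of the sample per patient. How often this would happen cannot be stated from the documents. Eligibility belongs in the protocol, so a statistical analysis plan cannot supply the missing item.

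**What to change.** Add to Inclusion criteria an item covering implanted electronic devices and metal implants in the stimulated region, with the exact wording and scope set by the investigators. In the description of the first visit, state that the item is checked before the first stimulation by one screening question and by review of the resting ECG. The question is needed because no medical history is listed and an ECG does not show orthopaedic metal. The visit chart already places the fitness test, and therefore the ECG, ahead of the initiation session, so the order of procedures need not change.

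The cost is one line in the criteria, one added question and possibly a few excluded patients.

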**Groups**:

All patients will receive the same evaluations and follow the same protocol.

We will include equal numbers of patients from different severity groups: GOLD II, III and IV.

**Sample size**

As this is an observational study, we will include 3 groups of 7 COPD patients with different severity (GOLD II, III and IV) giving a total of 21 patients.

**Study schedule**

Participation in this study involves 3 visits. The first and second visits (V1 and V2) will be separated by a day while the third visit (V3) will occur 7 days after V2. During these 7 days, the patient will be asked to carry out 5 sessions of electrical muscle stimulation training by himself, spread out as whenever he likes. He will be given the electrical stimulator and the electrodes during V2.

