**V2: Autonomous use of EMS, measure of pain perceived and of muscle fatigue**

The aim of this visit is to ensure that the patient can carry out electrical muscle stimulation in autonomy so that he will be able to use the apparatus at home. A full stimulation session will be carried out during which the patient will progressively take charge of the session. During electrical muscle stimulation, symptoms will be monitored (pain perception). The strength of the quadriceps will be tested before and after the session in order to measure the muscular fatigue caused by an initial EMS session. Finally, body composition will be determined during the course of this visit.

**V3: Assessment of EMS progression. Measure of pain perceived and of muscle fatigue at EMS intensity used during the sessions at home.**

The aim of this visit is to measure the pain perceived during a session of electrical muscle stimulation carried out at the EMS intensity that was used during the sessions at home. At the start of the session, the intensity of the stimulation applied will be that reached during visit 2, in order to compare the pain perceived for a given intensity, after 7 days of using the apparatus. Next, the patient will be asked to increase the intensity up to the level reached at home in order for us to calculate the intensity increase delta between V2 and V3. Throughout the course of this EMS session, the cardio-respiratory response will be measured using a portable “metabograph” fitted with a telemetric system (Oxycon mobile, Viasys). Furthermore, a blood sample will be taken before and after the session in order to measure systemic inflammation and oxidative stress levels. Lastly, muscular strength will be measured in order to determine the fatigue induced by this session.

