***Blood samples***

A nurse, member of our research team, will take two blood samples during visit 2.

**Blood test #1 – before the EMS session:** (maximum volume = 20mL)

1. A complete blood count (4mL)
2. Inflammatory proteins and oxidative stress (12mL)
3. **CRP:** An Enzyme-Linked Immunoabsorbent Assay (ELISA) will be used to measure CRP (C Reactive Protein), an acute phase inflammatory protein.
4. **IL-6:** An Enzyme-Linked Immunoabsorbent Assay (ELISA) will be used to measure IL-6 (Interleukin-6), an inflammatory cytokine produced by muscles and found at its highest levels during muscular contraction.
5. **AOPP:** Proteins are susceptible to damage by free radicals induced by oxidative stress. AOPP (Advanced Oxidation Protein Products) is monitored in the plasma and expressed as chloramine-T equivalents by measuring the absorbance in acidic conditions at a wavelength of 340 nm in the presence of potassium iodide.

**Blood test #2 – after the EMS session:** (volume = 12mL)

Inflammatory proteins and oxidative stress (12mL)

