**At home: five EMS sessions carried out autonomously at home**

During the seven days separating visits V2 and V3, the patient will be required to carry out 5 sessions at home. He will be asked to increase the EMS intensity as much as he can throughout one session and from one session to another, whilst staying beneath his pain threshold. In other words, he will have to increase the intensity frequently in order to always be at the maximum bearable intensity. For each session, the patient will have to write down the initial and final intensities along with the level of pain perceived for each. Throughout the week, we will maintain contact by phone (one initial phone call the day of the first session at home and then according to the patient’s needs) in order to answer any questions and/or solve any potential technical difficulties.

**Visit 3: Training session,** session as carried out by the patient at home.

Electrode placement

**Three electrodes on each leg:** two electrodes (50*50 mm) are placed on the skin by the lateral and the medial vastus of the quadriceps + one electrode (50*90 mm, double outlet) placed horizontally towards the top of the thigh, beneath the groin.

**
[figure not shown]

[figure not shown]
**

*Electrode placement for thigh rehabilitation*

*In this picture, the electrodes placed at the upper thigh are smaller models which will be replaced by electrodes of larger calibre, positioned side by side lengthwise (59*90 mm)*

**Electrode placement will be standardised** so as to lie by the lateral and the medial vastus motor points. The motor points will be identified for each patient individually, using a **pen electrode** that helps determine motor pathways and points of emergence.

Program

**Intermittent frequencies**: contraction at 50 Hz / “active” muscle relaxation at 5 Hz

- - - contraction 7 sec / relaxation 10 sec

**Time to reach contraction**: 3 seconds / time to relaxation: 1 second. Considering that the contraction is incomplete during the first two seconds of the contraction process, the cycles are 30%.

**Pulse width** = 400 µm

**The intensity** at which the patient begins to feel contraction of his thigh muscle is defined as the initial intensity; it is then progressively increased in order to reach the maximal bearable intensity.

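### Minor: a home session can fall hours before the V3 'before' measurements, and its timing is not among the diary items

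*Protocol*

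**What the plan says.** Study schedule: V3 is 7 days after V2, and in between the patient is asked to "carry out 5 sessions of electrical muscle stimulation training by himself, spread out as whenever he likes". The home-session section asks him to stay at the highest intensity he can bear. For each session, "the patient will have to write down the initial and final intensities along with the level of pain perceived for each"; date and time are not named. One phone call is planned, on the day of the first home session, and later calls depend on need.

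V2: quadriceps strength is "tested before and after the session in order to measure the muscular fatigue caused by an initial EMS session".

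V3: "muscular strength will be measured in order to determine the fatigue induced by this session", and "a blood sample will be taken before and after the session in order to measure systemic inflammation and oxidative stress levels". The Visit 3 list in the study scheme shows strength and blood both before and after the session. The Blood samples section differs: a nurse "will take two blood samples during visit 2".

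The Introduction states that there are no data on fatigue after a complete session in COPD patients, and hopes that such data will inform the minimum recovery delay between sessions.

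**The concern.** A before-to-after change measures the effect of one session only if the 'before' value is not still shifted by the previous one. Here the previous session is a demanding one, the patient chooses when it happens, and the protocol itself treats the recovery time as unknown. If residual fatigue were present, pre-session strength would start low and the measured fall could be too small. If inflammatory markers were still raised, the same could happen to the blood changes. Patients who trained on the morning of V3 and patients who had rested two days would then contribute changes that are not like for like.

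At stake are secondary objective 1 (fatigue), analysed under Objective #4, and secondary objective 2 (inflammation and oxidative stress), analysed under Objective #5. Objective #4 is touched only if V3 fatigue is used, since it names no visit. Objective #5 is touched only if blood is drawn at V3. A statistical analysis plan cannot repair this afterwards if the session times were never collected.

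**Working it through.** **Window.** The study scheme puts V2 at D0+1 and V3 at D0+8. 8 − 1 = 7 days, which agrees with the Study schedule. The full days between the visits are D0+2 to D0+7, that is 6.

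**Days from last home session to V3.** Assumption: at most one session per day, which the protocol does not state. The figures count possible arrangements of five sessions; they are not probabilities.

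| Usable days | Arrangements | 0 days | 1 day | 2 days | 3 days |
|---|---|---|---|---|---|
| 6 full days | C(6,5) = 6 | – | C(5,4) = 5 | 1 | – |
| plus rest of V2 day | C(7,5) = 21 | – | C(6,4) = 15 | C(5,4) = 5 | 1 |
| 6 full days plus V3 day before testing | C(7,5) = 21 | 15 | 5 | 1 | – |
| plus both | C(8,5) = 56 | C(7,4) = 35 | 15 | 5 | 1 |

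Without the V3 day, the gap is 1 or 2 days in 6 of 6 or in 20 of 21 arrangements. Only use of the V3 day brings it down to hours, and nothing in the text rules that out.

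**What the design already offers for strength.** V2 gives a before-and-after fatigue measure that only the 10–15 minute V1 initiation session precedes. V3-pre strength can also be compared with V2-pre. With 21 pairs (3 × 7, Sample size section), the 95% confidence half-width for the mean difference is

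t(0.975, 20)/√21 = 2.086/4.583 = 0.455 SD of the difference.

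The protocol gives no SD. For assumed SDs of 5, 10 and 15 percentage points, the half-width is 2.3, 4.6 and 6.8 points. The comparison is therefore informative for the group. It is only a partial check, because a strength gain from the home week could mask residual fatigue. Twitch force, measured "during a supramaximal magnetic stimulation of the femoral nerve", adds a version that does not depend on effort.

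**Blood.** If the V3 paragraph and the Visit 3 list govern, there is no earlier sample to compare with, and the recorded interval would be the main check. If the Blood samples section governs, both samples precede every home session and this part falls away.

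**Would analysis by interval help?** With n = 21, a correlation is distinguishable from zero at the two-sided 5% level only beyond about tanh(1.96/√18) = 0.43. With an interval that is mostly 1–2 days, such an analysis adds little.

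**The case against.** The strongest reply is that testing inside ongoing training is intended. V3 is described as a session like those at home, the implementation section speaks of effects within a rehabilitation program at the seventh session, and the secondary hypotheses treat fatigue over several sessions as part of the question. This stands as a reason not to demand full recovery before V3. It does not require a session on the same day, and it does not remove the need to know how long ago the last session was.

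The second reply is that the diary list need not be complete, and a form not shown may carry dates. That also stands: the interval may go unrecorded, but it is not shown to be.

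Some stronger readings are tempting but not supported:

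- **V3 fatigue is biased.** The documents give neither the size nor the direction of any carry-over.
- **The gap runs from hours to almost a week.** The upper end needs all five sessions done at once, which sits badly with wording that has them spread over the seven days.
- **A strength loss under 10% between visits cannot be detected in one patient.** The variation limit under maximum voluntary strength governs repeated contractions within one test. It is not a between-visit tolerance, and it does not apply to twitch force, for which the protocol cites earlier validation of reproducibility and sensitivity to change.
- **The main tolerance analysis is undermined.** The point concerns the V3 'before' strength and blood values. Recent training might also affect V3 pain at equal intensity, but nothing in the documents establishes that, and the point does not rest on it.

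**Conclusion.** The point holds as a minor one. The timing rule allows a demanding home session hours before the V3 'before' strength test, no rest is set, and session times are not among the named diary items. The V3 change may therefore not isolate the fatigue of that session. The same holds for the blood changes only if blood is drawn at V3.

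The likely extent is small: under one session per day the gap is mostly 1–2 days unless the V3 day is used. The V2 fatigue measure is free of home-session carry-over, although it describes an initial session and not one at the intensity reached at home. The conclusion rests on the text as written and on the stated one-per-day assumption for the counts.

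**What to change.** 1. In the Study schedule and the home-session section, instruct patients to do no home session on the day of V3 before testing. This ensures at least a night between the last home session and the tests. It does not guarantee recovery, since the recovery time is unknown.
2. Add the date and time of each home session to the diary, and confirm the last one with the patient at V3.
3. Report V3-pre against V2-pre strength, maximum voluntary and twitch, as a group-level check for residual fatigue.
4. Treat any display of V3 changes by hours since the last session as optional description. Patients choose the interval, so it may itself reflect tolerance.

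The cost is one diary entry and slightly less freedom. Six full days plus the rest of the V2 day remain for five sessions, so 21 one-per-day arrangements are still open.
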